**Figure 1 figure1:**
[figure not shown]
Consolidated Standards of Reporting Trials (CONSORT) flow diagram.

### Grouping and Dosage

Grouping and dosage are described in Table 2.

**Table 2 table2:** Grouping and dosage.

	Control group (polyherbal steam inhalation)	Intervention group (*dhoopana*; polyherbal nasal fumigation)
Participants, n	35	35
Name and details of the medication	*Arka* is prepared from *tulsi*, *vasa*, *nirgundi*, and *nilgiri*. In participants with mild symptoms, 2.5 ml *arka* is added to 500 ml of water, and in those with moderate to severe symptoms, 5 ml *arka* is added to 500 ml of water for steam inhalation.	*Dhoomvarti* (polyherbal wick) prepared from dry leaves of *tulsi*, *vasa*, *nirgundi*, and *nilgiri*.
Mechanism of delivery	Steam	Fumes
Duration	1 minute for mild symptoms and 1.5 minutes for moderate to severe symptoms.	1 minute for mild symptoms and 1.5 minutes for moderate to severe symptoms.
Route/mode of administration	Nostrils	Nostrils
Frequency	Twice daily	Twice daily

### Inclusion Criteria

Children of either sex aged between 7 to 14 years whose parents provide written consent for enrolling their child in the study will be included if they have had the common cold with features of *pratishyaya* for 7-10 days.

### Exclusion Criteria

Patients will be excluded if they have had the common cold for more than 10 days or if they have chronic allergic rhinitis, *dushta pratishyaya* (chronic rhinitis with complications), *raktaja pratishyaya* (a type of rhinitis with dominance of the blood element), *sannipataja pratishyaya* (rhinitis with involvement of all 3 elements), or infectious diseases such as tuberculosis. Patients will also be excluded if they have a cleft palate, a deviated nasal septum, or nasal polyps, or if they are hypersensitive to the trial drug or any of its ingredients.

### Drug Collection and Authentication

The raw material for the drug was purchased from a reliable source and authenticated and identified by the Department of Dravyaguna and Rasashastra. Details of the raw ingredients are provided in Table 3 and images are shown in Multimedia Appendix 1.

The *dhoomvarti* (polyherbal wick) for nasal fumigation and *arka* (for steam inhalation) from *tulsi*, *vasa*, *nirgundi*, and *nilgiri* leaves were prepared as per the classical methods and standard protocol at the Mahatma Gandhi Ayurveda College and Hospital and were analyzed in a pharmaceutical laboratory. The method of drug preparation is described in Figure 2.

*Arka* of the leaves of *tulsi*, *vasa*, *nirgundi*, and *nilgiri* was prepared by using a distillation process. Parents of the patients were counseled and trained regarding the administration of *dhoopana* and steam inhalation at their homes.

**Table 3 table3:** Latin name and family name of the herbs used for nasal fumigation and steam inhalation

Serial No.	Drug	Latin name	Family
1	*Tulsi*	*Ocimum sanctum* Linn	Lamiaceae
6	*Nirgundi*	*Vitex negundo* Linn	Verbenaceae
7	*Vasa*	*Adhatoda vasica* Nees	Acanthaceae
8	*Nilgiri*	*Eucalyptus globules* Labill	Myrtaceae

**Figure 2 figure2:**
[figure not shown]
Method of preparation of dhoomvarti.

### Outcomes

The outcomes are designed to compare the efficacy of *dhoopana* and polyherbal steam inhalation on *pratishyaya* with subjective and objective parameters.

#### Subjective Criteria

Signs and symptoms of *pratishyaya* will be evaluated with the TNSS, illustrated in Table 4.

**Table 4 table4:** Total Nasal Symptom Score (TNSS).

Symptom and domain			Score
**Symptoms**			
	**Rhinorrhoea**		
		No symptoms	0
		Aware but not troubled (mild)	1
		Troublesome but does not interfere with normal day-to-day activities or sleeping habits (moderate)	2
		Interferes with normal day-to-day activities or sleeping habits (severe)	3
	**Nasal itching**		
		No symptoms	0
		Aware but not troubled (mild)	1
		Troublesome but does not interfere with normal day-to-day activities or sleeping habits (moderate)	2
		Interferes with normal day-to-day activities or sleeping habits (severe)	3
	**Nasal obstruction**		
		No symptoms	0
		Aware but not troubled (mild)	1
		Troublesome but does not interfere with normal day-to-day activities or sleeping habits (moderate)	2
		Interferes with normal day-to-day activities or sleeping habits (severe)	3
	**Sneezing**		
		No symptoms	0
		Aware but not troubled (mild)	1
		Troublesome but does not interfere with normal day-to-day activities or sleeping habits (moderate)	2
		Interferes with normal day-to-day activities or sleeping habits (severe)	3
**Additional symptoms as per Ayurveda texts**			
	* **Sirashoola** * **(headache)**		
		No headache	0
		Occasional headache	1
		Frequent headache	2
		Continuous headache	3
	* **Aruchi** * **(loss of appetite)**		
		Absent	0
		Present	1
	* **Kasa** * **(cough)**		
		No cough	0
		Occasional cough	1
		Moderate cough	2
		Continuous cough with throat and chest pain	3

#### Objective Criteria

The modified cold spatula test will be used to measure nasal patency in rhinitis. The test is done to study the area of fogging associated with a nasal obstruction and compare the pre- and posttreatment outcomes. The patients are asked to breathe normally over a polished stainless steel plate, and the extent of fogging is marked with a marker pen. The magnitude of fogging is then measured with a transparent graph sheet marked with a central red line at 50 mm on the x-axis, dividing the graph into 2 equal parts with corresponding right and left areas of fogging.

### Sample Size

A comparative pilot study was performed with 20 patients, including 10 patients in 2 groups, to evaluate the efficacy of *dhoopana* for rhinitis in comparison with polyherbal steam inhalation. Based on the results of that study, the minimum sample size for this study was calculated by using the following formula of proportion:

The parameters related to sample size were as follows: α=.05; β=.2; proportion in group 1=0.60; proportion in group 2=0.90; ratio (group 2/group 1)=1; minimum sample size needed for group 1=32; and minimum sample size needed for group 2=32. The minimum total sample size needed was 64, and the minimum total number of patients to be enrolled was 35 in each group (including a 10% withdrawal rate).

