**Methods:**

A total of 70 participants fulfilling the inclusion criteria were selected and distributed into 2 groups of 35 each. The intervention group received *dhoopana* and the control group received polyherbal steam inhalation, both twice daily for 7 days. The primary outcome measure was the change in Total Nasal Symptom Score and a modified cold spatula test. At the same time, the association between *prakriti* (body constitution) and the prevalence of *pratishyaya* in children was analyzed as a secondary outcome. Assessments were performed on days 3, 5, and 7, with a follow-up time of 28 days. Appropriate descriptive and inferential statistics will be used for data analysis.

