### Data Analysis

Data will be analyzed by using appropriate descriptive and inferential statistics. Quantitative variables will be analyzed with the Student *t* test and subjective parameters will be analyzed with the Wilcoxon signed test and Mann-Whitney *U* test. Alternate statistical methodologies may be applied if deemed necessary.

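### The stated 80% power comes from a two-proportion calculation and applies to neither primary outcome as the article plans to analyse it

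*Protocol article*

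**What the plan says.** Sample Size (Methods) refers to a 20-patient pilot, 10 per group, and states that "the minimum sample size for this study was calculated by using the following formula of proportion". The inputs are "α=.05; β=.2; proportion in group 1=0.60; proportion in group 2=0.90", with "ratio (group 2/group 1)=1", and the result is "minimum sample size needed for group 1=32; and minimum sample size needed for group 2=32". The text does not say what is being counted in these proportions, or which treatment is group 1.

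The Abstract (Methods) states: "The primary outcome measure was the change in Total Nasal Symptom Score and a modified cold spatula test". Primary Objectives agrees, covering signs and symptoms, the duration of TNSS relief, and nasal obstruction on the spatula test. Under Outcomes, TNSS is a set of graded symptom items listed as subjective, and the spatula test is an objective measurement of fogging read from a graph sheet.

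Data Analysis states: "Quantitative variables will be analyzed with the Student" t test, and assigns subjective parameters to the Wilcoxon signed and Mann-Whitney tests. It adds that other methods may be used if needed. No comparison of proportions is named.

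Results reports 70 enrolled, 4 withdrawn and 66 to be analysed. Withdrawal Criteria and Stoppage puts 2 withdrawals in each group, so 33 per arm.

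**The concern.** A power statement describes one test of one outcome at one assumed effect. Here the calculation assumes a binary outcome and a test of two proportions, while the primary outcomes are a score change and an area, compared by rank and t tests. Nothing in the article converts 60% against 90% into TNSS points or fogging area.

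A reader will naturally take α=.05 and β=.2 as describing the primary analysis. They do not, so the reader cannot tell what difference in TNSS or fogging the trial could detect. That matters because the article expects to report the two treatments as equally effective, and such a claim is only as strong as the trial's ability to resolve a difference on the outcome concerned. The mismatch is separate from the lack of an equivalence margin: it would remain in a superiority trial.

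**Working it through.** **1. Reproducing the article's figure.** Inputs from Sample Size: p1 = 0.60, p2 = 0.90, α = 0.05, β = 0.2, ratio 1. The article does not give the sidedness. I take two-sided, no continuity correction, pooled variance under the null, with mean proportion 0.75.

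n per group = [z(0.975)·√(2·0.75·0.25) + z(0.80)·√(0.60·0.40 + 0.90·0.10)]² / (0.90 − 0.60)²

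= [1.960·√0.375 + 0.842·√0.33]² / 0.09 = (1.200 + 0.483)² / 0.09 ≈ 31.5, rounded up to 32.

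This matches the stated 32. Power for this test is 80.6% at 32 per group and 81.9% at 33. The formula itself is missing from the extracted text, but the stated inputs are enough to identify a test of a difference in proportions. (A one-sided test with continuity correction also gives 32. That is still a test of proportions, so the point does not depend on the choice.)

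**2. Setting the sections side by side.**

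| Item | Sample Size | Outcomes and Data Analysis |
|---|---|---|
| Quantity | proportion, 0.60 v 0.90 | TNSS change; fogging area |
| Scale | binary | graded score; measured area |
| Test | two proportions | Mann-Whitney for subjective, t test for quantitative parameters |
| Effect | 30 percentage points | none given in points or area |

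The quantity, the scale and the test all differ.

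**3. What 33 per arm gives under the planned tests.** The article states no SD and no expected difference, so power can only be shown over an assumed range of standardised differences d (difference divided by SD). For the two-sided 5% t test, power comes from the noncentral t distribution with 64 degrees of freedom and noncentrality d·√(33/2) = 4.062·d.

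| d (SD units) | Power, t test |
|---|---|
| 0.3 | 22% |
| 0.5 | 52% |
| 0.70 | 80% |
| 0.8 | 89% |
| 1.0 | 98% |

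For Mann-Whitney with normal data the relative efficiency is 0.955, so the difference detectable with 80% power is about 0.70/√0.955 = 0.72 SD. At 0.70 SD its power is about 78%.

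**4. Can 60% v 90% be translated?** Only under a further assumption. If the proportions came from cutting a normal score with equal SDs at one threshold, the implied shift would be z(0.90) − z(0.60) = 1.282 − 0.253 = 1.03 SD, where the t test has about 98% power. The article does not state this link, and a smaller true shift would fall in the lower rows of the table.

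**The case against.** The strongest defence has four parts.

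- **The arithmetic is right.** This stands. The fault is a mismatch between sections, not a calculation error.
- **A responder definition may exist in the pilot report, the thesis or a fuller protocol.** This also stands as far as it goes, and the missing definition alone would be a weak point in a condensed article. But the point rests on what is printed: the sizing quantity, the primary outcomes and the tests do not match. A definition elsewhere would not change the stated primary outcomes or tests.
- **Data Analysis leaves room for other methods, and binary items do exist.** Loss of appetite is scored absent or present in Table 4, and the secondary objectives concern prevalence. So it would be wrong to say that the article contains nothing binary. None of this is a primary responder endpoint or is tied to 60% v 90%, and an open clause naming no method cannot be the basis of a stated power.
- **Enrolment is complete and confidence intervals will show the precision achieved.** True. It limits the consequence to how the trial is described and interpreted.

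A reader might go further and infer that the trial is underpowered, or that a correct statement must look worse. The article does not support this. With no SD or difference given, power under the planned tests could lie on either side of 80%, and analysing a score on its own scale often has more power than dichotomising it.

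**Conclusion.** The point holds as an inconsistency. The 32 per group is correct for a two-sided comparison of 60% with 90%, but that comparison is not among the planned primary analyses, so the 80% power applies to neither TNSS change nor fogging area. Power for the planned tests cannot be determined from the article. Over an assumed range of 0.3 to 1.0 SD it runs from 22% to 98% for a t test with 33 per arm, reaching 80% at about 0.70 SD (about 0.72 SD for Mann-Whitney). These figures assume normal data, equal SDs, 33 analysed per arm and a two-sided 5% level. They describe detection of a difference and say nothing about power to show equivalence, which is a separate matter.

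**What to change.** - In Sample Size, say that the 80% power refers to a comparison of 60% with 90% on a binary outcome, and stop presenting it as the power for the primary outcomes.
- For both TNSS change and fogging area, state the difference that 33 per arm can detect with 80% power under the test assigned to each: about 0.70 SD by t test and about 0.72 SD by Mann-Whitney with normal data. On the article's own classification, TNSS falls to the rank test and fogging area to the t test. Convert these to TNSS points and area units with the pilot SDs, and note that SDs from 10 per arm are imprecise.
- Do not set an equivalence margin from the achieved sample size. A detectable difference is not a margin; any margin must be justified on clinical grounds and fixed before the analysis.
- If the pilot's responder definition is kept, define it and list it as a secondary outcome, with a confidence interval for the difference in proportions.

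The cost is wording only. The stated power may move in either direction, and no extra patients are needed.

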### Hypothesis

The alternate hypothesis is that *dhoopana* has equivalent efficacy to polyherbal steam inhalation in reducing the signs and symptoms of *pratishyaya* in children aged 7-14 years. The null hypothesis is that *dhoopana* does not have equivalent efficacy as polyherbal steam inhalation in reducing the signs and symptoms of *pratishyaya* in children aged 7-14 years.

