### Trial Design

This will be a randomized, reference, controlled, open-label equivalence clinical study. A total of 70 patients have been recruited for the study.

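### The 32 per group is sized to detect 60% v 90%, not to show equivalence, so β=.2 is not the power of the trial's own hypothesis

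*Protocol article*

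**What the plan says.** The article's Trial Design section calls the trial a "randomized, reference, controlled, open-label equivalence clinical study". In the Hypothesis section the alternative is that dhoopana "has equivalent efficacy to polyherbal steam inhalation in reducing the signs and symptoms of" pratishyaya, and the null is that it "does not have equivalent efficacy as polyherbal steam inhalation in reducing the signs and symptoms of" pratishyaya. The Conclusions of the Abstract and the Discussion both expect the two treatments to be equally effective.

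The Sample Size section takes its inputs from a pilot of 20 patients, 10 per group: "α=.05; β=.2; proportion in group 1=0.60; proportion in group 2=0.90; ratio (group 2/group 1)=1; minimum sample size needed for group 1=32". The same minimum is given for group 2, making 64 in total, and enrolment is set at 35 per group to allow for 10% withdrawal. The section does not say which arm is group 1 or what event the proportions count.

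The Abstract names change in TNSS and the modified cold spatula test as primary outcomes. Data Analysis names the Student t, Wilcoxon and Mann-Whitney tests. Results reports 70 enrolled and 4 withdrawn (2 per group, according to Withdrawal Criteria and Stoppage), which leaves 33 per arm.

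**The concern.** A β belongs to a particular alternative hypothesis. In an equivalence trial the alternative is that the treatments differ by less than a margin, and power is the chance of showing this when they really are alike. Here the planning alternative is a true gap of 30 points, the reverse of what the trial hopes to show. A reader who takes β=.2 as the power of this trial will credit it with an 80% chance of establishing equivalence that was never calculated.

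The named tests are all tests of difference. In a trial labelled as equivalence and presented with β=.2, a non-significant result could easily be taken as proof that fumigation works as well as steam. The Discussion would carry that conclusion into general pediatric practice. With about 33 children per arm, a non-significant result can coexist with a large true difference.

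**Working it through.** **1. Reproduce the stated figure.** Inputs from Sample Size: p1 = 0.60, p2 = 0.90, α = .05, β = .2, ratio 1. The mean rate is 0.75. The two-sided difference formula with pooled variance is

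n = [1.96·√(2·0.75·0.25) + 0.8416·√(0.60·0.40 + 0.90·0.10)]² / 0.30²

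= [1.2002 + 0.4835]² / 0.09 = 2.8349 / 0.09 = 31.5, rounded up to **32**.

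This is the stated number, and power at n = 32 is 80.6%. Other versions of the difference formula give 38 (two-sided, continuity-corrected), 25 (one-sided), 32 (one-sided, continuity-corrected) and 29 (two-sided, unpooled). Both versions that return 32 are difference calculations.

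**2. Could 0.30 have been meant as a margin?** The normal-approximation equivalence formula for a true difference of zero, 80% power and one-sided 5% per test is

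n = (1.645 + 1.282)² · 2p(1−p) / margin².

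With margin 0.30 it gives 46, 36 and 18 per arm at common rates of 0.60, 0.75 and 0.90. At one-sided 2.5% per test it gives 57, 44 and 22. None is 32, and nothing in the section calls 0.30 a margin.

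**3. Equivalence power at the achieved size.** The number per arm is 35 − 2 = 33. Assumptions not in the article: equal true rates of 60%, 75% or 90%; equivalence claimed when the 90% Wald interval for the difference lies inside the margin; margins of ±15 to ±30 points. Power is found by enumerating two independent binomials of size 33.

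| Margin | Both 60% | Both 75% | Both 90% |
|---|---|---|---|
| ±15 points | 0% | 1% | 32% |
| ±20 points | 6% | 22% | 73% |
| ±25 points | 31% | 52% | 89% |
| ±30 points | 62% | 78% | 98% |

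**4. Equivalence power if the planning rates were true.** With 60% v 90% and 33 per arm, the same enumeration gives 0.5% at ±20 points and about 6% at ±30.

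**5. Size needed for 80% equivalence power.** By the formula in step 2, a ±20-point margin needs 103, 81 and 39 per arm at common rates of 60%, 75% and 90%. A ±15-point margin needs 183, 143 and 69.

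**The case against.** The arithmetic in Sample Size is right for the question it answers. The section prints β=.2, not a claim of 80% power for equivalence. The formula is absent from the text at hand. A margin may stand in the full protocol or in an analysis plan that is not shown, so its absence from the article is not in itself an error. All of this stands, but it does not reach the point: the inputs that are printed yield 32 as a calculation to detect a difference, and a margin stated elsewhere could not change what that β refers to.

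A reader might infer that the trial is too small for equivalence at any ordinary margin. The documents do not support that. If both true rates were near 90%, which is the article's own upper proportion, 33 per arm would give 89% power at ±25 points and 98% at ±30. Even at 75%, power at ±30 is 78%. Without a margin and a common rate, no single verdict on size is possible.

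A reader might also infer that the powers above describe the primary analysis. They do not. The binary event is undefined, and the named primary outcomes are change in TNSS and the spatula test. Equivalence power for those cannot be computed from the article. For the same reason, planning rates of 60% and 90% contradict equivalence only for that unnamed event and for a margin below 30 points.

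**Conclusion.** Wrong as written. The hypothesis and the sample-size method do not match: the trial is declared an equivalence study, while its 32 per group comes from a calculation to detect 60% v 90% with no margin among the inputs. This rests only on the printed inputs and on the exact reproduction of 32.

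The size of the consequence is conditional. Under the stated assumptions, equivalence power with 33 per arm runs from 0% (±15 points, rates of 60%) to 98% (±30 points, rates of 90%), and it is at most about 6% for margins up to ±30 if the planning rates hold. The range shows that β=.2 says nothing reliable about equivalence. It is not an estimate of the power for TNSS or the spatula test.

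**What to change.** No more patients are needed.

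- **Sample Size:** state that 32 per group gives 80% power, at two-sided 5%, to detect 60% v 90% on the binary event used; name that event; and say that the calculation does not power the equivalence hypothesis.
- **Margin:** state an equivalence margin on the primary outcome itself, change in TNSS. Fix it before the outcome data are examined and, if that is so, label it as set after enrolment. This matters more because the trial is open-label.
- **Power or precision:** report the equivalence power, or the expected width of the confidence interval, for change in TNSS at about 33 per arm. A power for the binary event placed beside a TNSS margin would create a new mismatch.
- **Hypothesis and Data Analysis:** conclude equivalence only if the confidence interval for the between-group difference lies wholly inside the margin, and otherwise report the result as inconclusive. State that a non-significant t or Mann-Whitney test will not be read as equivalence.

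The cost is wording, the work of justifying a margin, and a less favourable statement of power.

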### Data Collection Tools

This study will use the *Ayurveda Samhitas* (a textbook on Ayurveda), modern texts, and an online search of PubMed and Google Scholar. The polyherbal *dhoomvarti* will be prepared from a powder of *tulsi*, *vasa*, *nirgundi*, and *nilgiri*. The polyherbal *arka* will be prepared from *tulsi*, *vasa*, *nirgundi*, and *nilgiri*. The study will also use a case record form, patient information sheet, and written informed consent form.

### Data Analysis

Data will be analyzed by using appropriate descriptive and inferential statistics. Quantitative variables will be analyzed with the Student *t* test and subjective parameters will be analyzed with the Wilcoxon signed test and Mann-Whitney *U* test. Alternate statistical methodologies may be applied if deemed necessary.

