## Methods

### Recruitment

The patients were selected from the outpatient and inpatient departments of the Department of Kaumarabhritya (Ayurvedic pediatrics) of Mahatma Gandhi Ayurveda College, Hospital & Research Centre and from the surrounding region. After initial screening, the patients were randomized using computer-generated random numbers into 2 groups; the control group (polyherbal steam inhalation) and the intervention group (polyherbal nasal fumigation). All baseline parameters were recorded at the start of the study. Both groups underwent treatment for 7 days. All the parameters were recorded on the third, fifth, and seventh days, with a follow-up of 28 days after the treatment period. Patients were advised to drink warm water and stay away from cold and sour items. Patients were given regular counseling and reminders through calls or messages to follow the rules and regulations of the trial.

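### The named tests for change in TNSS and fogging take no baseline covariate; they are valid, but a prespecified baseline-adjusted difference with a confidence interval would usually be more precise

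*Protocol article*

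**What the plan says.** The abstract defines the primary outcome: "The primary outcome measure was the change in Total Nasal Symptom Score and a modified cold spatula test". Under Objective Criteria, fogging is measured to "compare the pre- and posttreatment outcomes". Under Subjective Criteria, signs and symptoms "will be evaluated with the TNSS".

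The Data Analysis section assigns the tests by type of variable: "Quantitative variables will be analyzed with the Student" *t* test, and "subjective parameters will be analyzed with the Wilcoxon signed test and Mann-Whitney" *U* test. Fogging area therefore falls to the *t* test and TNSS to the rank tests. The section names no covariate, visit or confidence interval. It does not say whether the between-group tests are run on change or on post-treatment scores. It ends with "Alternate statistical methodologies may be applied if deemed necessary".

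The baseline data exist. Recruitment states: "All baseline parameters were recorded at the start of the study". Assessments follow on days 3, 5 and 7, with a 28-day follow-up. Trial Design calls the study an open-label equivalence study. Of 70 children, 2 withdrew in each group, and Results says that 66 will be analysed.

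**The concern.** An equivalence claim rests on how precisely the difference between arms is estimated, and 33 children per arm is few. Subtracting the baseline, as a change score does, is a crude use of it. Unless the correlation between baseline and outcome is close to 1, children who start worse tend to fall further, so a chance difference in baseline severity carries into the difference in mean change. Regressing the outcome on its baseline uses the same data better. For TNSS there is a further limit: a rank test alone gives a p-value, not an estimate with an interval, and an equivalence claim needs the latter.

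**Working it through.** **The plan's own figure.** Sample Size gives 32 per group for proportions 0.60 and 0.90, α = 0.05, β = 0.2. With pooled variance, two-sided and without continuity correction:

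n = [1.96·√(2·0.75·0.25) + 0.8416·√(0.60·0.40 + 0.90·0.10)]² / 0.30² = (1.200 + 0.483)² / 0.09 ≈ 31.5, so 32.

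The figure reproduces. It rests on proportions, so it says nothing about the precision of a mean TNSS or fogging difference.

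**Inputs for the comparison.** n = 35 − 2 = 33 per arm (Withdrawal Criteria and Stoppage; Results). The SDs and the baseline-outcome correlation r are not given. I assume equal SDs at baseline and after treatment, and I vary r.

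**Variance of the between-group difference**, in units of 2·SD²/n:
- unadjusted post-treatment score: 1
- unadjusted change: 2(1 − r)
- baseline-adjusted (ANCOVA): 1 − r²

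Adjusted over change is (1 − r²) / [2(1 − r)] = (1 + r)/2, which is 0.65, 0.75 and 0.85 at r = 0.3, 0.5 and 0.7.

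**Small-sample price.** Estimating the slope multiplies the width by √(1 + 1/(2n − 4)) = √(1 + 1/62). The lost degree of freedom multiplies it by 1.99834/1.99773 (t on 63 against 64 df). Together this is 1.0083, or about 0.8%.

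**Relative width of the 95% interval, adjusted against unadjusted:**

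| r (assumed) | vs change, √((1 + r)/2) | vs change, × 1.0083 | vs post-treatment score, √(1 − r²) × 1.0083 |
|---|---|---|---|
| 0 | 0.707 | 0.713 | 1.008 |
| 0.3 | 0.806 | 0.813 | 0.962 |
| 0.5 | 0.866 | 0.873 | 0.873 |
| 0.7 | 0.922 | 0.930 | 0.720 |
| 0.9 | 0.975 | 0.983 | 0.440 |

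**Break-even.** Against the post-treatment score, adjustment pays once r exceeds √(1 − 1/1.0083²) ≈ 0.13. Against change, it is narrower on average until r reaches 2/1.0083² − 1 ≈ 0.97.

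**Simulation**, 20,000 trials per value of r, agrees. The adjusted interval was narrower than the change interval in 99.6% of trials at r = 0.5, 95.5% at r = 0.7 and 66% at r = 0.9. It was narrower than the post-treatment interval in 20% of trials at r = 0, 85% at r = 0.3 and 99.5% at r = 0.5.

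**Chance imbalance.** The difference in baseline means has SD √(2/33) = 0.246 SD. An imbalance of that size shifts the expected change difference by (1 − r) × 0.246, that is 0.17, 0.12 and 0.07 SD at r = 0.3, 0.5 and 0.7. At r = 0.5 the half-width of the change interval is 1.998 × 0.246 × √(2 × 0.5) ≈ 0.49 SD, so the shift is about a quarter of it. The unadjusted standard error already counts this variation. It is the same loss of precision seen from another side, not an added bias.

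**The case against.** Unadjusted tests are valid under randomisation. A condensed article may leave covariates to an analysis plan that is not shown, and this one leaves other methods open. That stands to the extent that nothing here is an error. It does not dispose of the point, because the article does choose tests for the primary measures, and an open clause in an open-label trial does not prespecify a better one.

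The size of the gain is also open to challenge, and rightly. The ratio (1 + r)/2 compares least-squares ANCOVA with a mean change score. It applies to fogging if change is tested, but to TNSS only if TNSS is modelled as a numeric score; it is not the gain over Mann-Whitney. TNSS is a bounded sum of ordinal items that may reach its floor as a cold resolves, so linearity is a real assumption.

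A reader might infer more than the text supports:
- That the tests are run visit by visit. The article names no visit.
- That randomisation was simple. Recruitment mentions only computer-generated random numbers, which neither states nor excludes blocking or stratification.
- That severity-dependent exposure biases the comparison. Table 2 gives the same duration rule in both arms ("1 minute for mild symptoms and 1.5 minutes for moderate to severe symptoms"). The control arm's *arka* volume also varies with severity. Rules tied to severity in this way do not by themselves bias an unadjusted comparison of randomised arms.

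**Conclusion.** The point holds as a recommendation on efficiency. The named tests leave a recorded baseline unused except, at most, by subtraction. Against unadjusted change, the stated outcome, adjustment would narrow the interval by about 19% to 7% for r from 0.3 to 0.7. If post-treatment scores are what is tested, the gain is 4% at r = 0.3, 13% at r = 0.5 and 28% at r = 0.7, with none below about r = 0.13. All of this assumes equal SDs and a correlation that the article does not report.

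It would be too strong to say that adjustment removes chance imbalance or is free. It corrects the estimate only for the modelled baseline, and only as far as the model fits. Nor would it make the analysis a test of equivalence: the article states no margin, and adjustment cannot supply one.

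**What to change.** Before the data are examined, record in a dated document, for TNSS and for total fogging area, that the primary comparison is the between-group difference with a confidence interval, adjusted for that outcome's own baseline. ANCOVA at one chosen visit would do, as would a mixed model over the scheduled visits with treatment, visit, their interaction and baseline by visit. Keep Mann-Whitney as a sensitivity analysis because TNSS is a bounded ordinal sum. If outcomes have already been compared by arm, report the adjusted analysis as not prespecified.

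No new data are needed. With ANCOVA the price is one degree of freedom, about 0.8% in interval width if baseline turns out to be uninformative, and the linearity assumption. The equivalence margin and the primary time point must be set and justified separately; until they are, a narrower interval has nothing to be judged against.
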